#### Exclusion criteria

2.3.2

1) Drug addiction, alcoholism, and mental illnesses (including comprehension difficulties, full aphasia, and severe cognitive disorders);2) Serious systemic illnesses, such as cardiovascular or cerebrovascular disease, or severe abnormalities of the central nervous system; these conditions will be identified through the participant’s self-report during the screening interview and, upon the participant’s consent to access existing medical records, confirmed by medical records or previous diagnostic imaging studies.3) A history of craniocerebral trauma or other documented organic neurological abnormalities;4) Abnormal tympanometric findings, acoustic reflection test findings, otoscopic examination findings or abnormal DPOAEs;5) Ménière’s disease, otosclerosis, acoustic neuroma, abrupt sensorineural hearing loss, conductive and mixed hearing loss, or other conditions affecting the inner ear or auditory nerve;6) History of objective tinnitus, somatosensory tinnitus, external ear canal infection, acute or chronic otitis media, or other conditions affecting the outer or middle ear;7) Participants who are currently receiving or have recently received other tinnitus-related interventions, including pharmacological treatment, sound therapy, psychological interventions, or other acupuncture treatments;8) Unable to tolerate acupuncture treatments due to various reasons, as well as pregnant and lactating women.

### Inclusion and exclusion criteria of healthy volunteers

2.4

#### Inclusion criteria

2.4.1

1) Pure-tone average hearing threshold <20 dB HL in both ears, with no individual frequency exceeding 30 dB HL;2) Normal tympanometric findings, acoustic reflection test findings, otoscopic examination findings and normal DPOAEs.3) Aged between 18 and 60 years, inclusive, any sex;4) Both tympanic membranes are intact and the external auditory canal is clear;5) Sufficient expressive and comprehensive language skills, adequate cognitive function, and the capacity to collaborate with the study’s experimental procedures;6) Signing the informed consent form and not taking part in any other interventional clinical trials at this time.

#### Exclusion criteria

2.4.2

1) Pregnant or breastfeeding women, and those who have a request for childbearing within the next 6 months;2) History of head trauma, or history of persistent tinnitus (defined as tinnitus lasting >5 min, occurring more than once per week, or lasting >3 months);3) Abnormal tympanometric findings, acoustic reflection test findings, otoscopic examination findings or abnormal DPOAEs;4) Any condition that precludes ABR testing, such as the existence of metallic implants in the body;5) Participation in any ongoing interventional clinical trials.

If a person satisfies all inclusion requirements and none of the exclusion requirements, they will be qualified to take part in the study. Written informed consent will be obtained from all participants prior to enrollment. Participants will be informed of the study purpose, procedures, potential risks and benefits, and their right to withdraw at any time without consequence.

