### Design overview

2.1

This study adopts a hybrid two-part design comprising a matched case–control observational component and a self-controlled interventional component.

In the first component, patients with chronic tinnitus will be compared with age- and sex-matched healthy controls to identify baseline differences in auditory neurophysiological characteristics, including ABR parameters. In the second component, patients with chronic tinnitus will receive a standardized acupuncture intervention and will be followed longitudinally to evaluate changes in subjective tinnitus severity and auditory neurophysiological function. Healthy controls will also undergo two ABR assessment over a comparable time interval to estimate test–retest variability and distinguish treatment-associated changes from normal measurement variability.

There is no sham acupuncture control group in this study. We acknowledge that placebo effects, expectation-related responses, and other non-specific effects associated with acupuncture cannot be completely excluded and may influence the interpretation of treatment-associated changes. To minimize the placebo effect, a strict assessor-blinded design will be adopted. The ABR waveforms will be anonymized and coded before interpretation, with audiologists blinded to both group allocation and time points. Clinical scale interviewers will be blinded to time point, and data analysts will work on a fully coded dataset until the final analysis is locked.

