
**Table 1 tab1:** SPIRIT schedule of enrollment, interventions, and assessments.

	Study period							
	Enrolment	Allocation	Treatment period				Post-treatment	Follow-up
TIMEPOINT (week)	Week −1(T0)	Week 0	W1	W2	W3	W4	W5 (T1)	W13 (T2: 8-week FU)
Enrolment								
Eligibility screen	X							
Informed consent	X							
Demographic/medical history	X							
Allocation		X						
Interventions								
Acupuncture (10 sessions, 3×/week)			X	X	X	X		
Assessments								
ABR parameters	X						X	
Pure-Tone Threshold testing	X							
Tympanometry & Acoustic reflex testing	X							
DPOAEs	X							
Otoscopic examination	X							
THI	X						X	X
TEQ	X						X	X
Loudness/Annoyance VAS	X						X	X
Adverse events			X	X	X	X	X	

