#### Inclusion criteria

2.3.1

1) Diagnosis of bilateral chronic subjective tinnitus (including primary and secondary tinnitus, as well as cochlear and central cases), with a duration of at least 6 months, and a score of at least 16 on the Chinese version of the THI scale (mild) (30);2) Pure-tone average hearing threshold (PTA) < 20 dB HL in both ears, with no individual frequency exceeding 30 dB HL (31);3) Normal tympanometric findings, acoustic reflection test findings, sotoscopic examination findings and normal Distortion product otoacoustic emissions (DPOAEs);4) Aged between 18 and 60 years, inclusive, any sex;5) Both tympanic membranes are intact and the external auditory canal is clear;6) Sufficient expressive and comprehensive language skills, adequate cognitive function, and the capacity to collaborate with the study’s experimental procedures;7) Signing the informed consent form and not taking part in any other interventional clinical trials at this time.

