#### Treatment course

2.6.1

All chronic tinnitus patients will receive a total of 10 acupuncture sessions, administered once every 2 days (three times per week) over a period of 4 weeks. Based on our prior research and clinical experience using acupuncture to treat tinnitus, we selected a total of 10 acupuncture sessions (33, 34). These methods are thought to be representative and appropriate for assessing acupuncture’s effectiveness in treating persistent tinnitus.

Patients will be observed at week eight after completing 10 sessions in order to more fully assess the long-term efficacy of acupuncture treatment.

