##### Acupuncture points prescription

2.6.2.1

Based on the clinical expertise of senior acupuncturists and the results of earlier relevant investigations, the acupoint prescription for this study was created (35). The selected acupoints are as follow: Yifeng (bilateral), Tinggong (bilateral), Tinghui (bilateral), Zhongwan, Xiawan, Qihai, Guanyuan, Yindu (bilateral), Shangqu (bilateral), Huaroumen (bilateral). Licensed acupuncturists with over 10 years of clinical experience will deliver all treatments. Before the experiment, all practitioners will receive standardised instructions to ensure protocol adherence. A brochure outlining the standardized operating procedures will be provided to each practitioner. Table 2 summarizes the precise positions of each acupoint, which will be identified in accordance with the WHO Standard Acupuncture Point Locations (36).

**Table 2 tab2:** Acupoint positions.

Acupoints	Position
Yifeng (TE17)	In the anterior region of the neck, posterior to the ear lobe, in the depression anterior to the inferior end of the mastoid process.
Tinggong (SI19)	On the face, in the depression between the anterior border of the centre of the tragus and the posterior border of the condylar process of the mandible.
Tinghui (GB2)	On the face, in the depression between the intertragic notch and the condylar process of the mandible.
Zhongwan (CV12)	On the upper abdomen, 4 B-cun superior to the centre of the umbilicus, on the anterior median line.
Xiawan (CV10)	On the upper abdomen, 2 B-cun superior to the centre of the umbilicus, on the anterior median line.
Qihai (CV6)	On the lower abdomen, 1.5 B-cun inferior to the centre of the umbilicus, on the anterior median line.
Guanyuan (CV4)	On the lower abdomen, 3 B-cun inferior to the centre of the umbilicus, on the anterior median line.
Yindu (KI19)	On the upper abdomen, 4 B-cun superior to the centre of the umbilicus, 0.5 B-cun lateral to the anterior median line.
Shangqu (KI17)	On the upper abdomen, 2 B-cun superior to the centre of the umbilicus, 0.5 B-cun lateral to the anterior median line.
Huaroumen (ST24)	On the upper abdomen, 1 B-cun superior to the centre of the umbilicus, 2 B-cun lateral to the anterior median line.

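### The planned-childbearing exclusion is printed for the untreated healthy controls but not for the tinnitus patients, who are the group receiving acupuncture

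*Protocol article*

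**What the plan says.** The article prints a separate itemised eligibility list for each group.

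- **Healthy controls** (section 2.4.2, item 1) are excluded if they are "Pregnant or breastfeeding women, and those who have a request for childbearing within the next 6 months".
- **Tinnitus patients** (section 2.3.2, item 8) are excluded if "Unable to tolerate acupuncture treatments due to various reasons, as well as pregnant and lactating women". No other patient item deals with pregnancy.
- The age and sex criterion is the same in both lists (sections 2.3.1 and 2.4.1): "Aged between 18 and 60 years, inclusive, any sex".
- The entry rule at the end of section 2.4.2 reads: "If a person satisfies all inclusion requirements and none of the exclusion requirements, they will be qualified to take part in the study".

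On exposure, section 2.6.1 states that "All chronic tinnitus patients will receive a total of 10 acupuncture sessions". For controls, section 2.1 says "Healthy controls will also undergo two ABR assessment over a comparable time interval" and assigns them no treatment. Table 1, "SPIRIT schedule of enrollment, interventions, and assessments", marks the eligibility screen once, at Week −1, acupuncture in W1 to W4, the post-treatment assessment (T1) at W5 and the follow-up (T2) at W13.

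**The concern.** A rule about intended pregnancy looks ahead: it keeps out someone who does not yet meet the pregnancy exclusion but may soon do so. Here it is attached to the group that has measurements only and is absent for the group that is treated. Within the article the placement looks reversed, and no reason is offered.

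What is at stake is participant protection and the coherence of the eligibility rules. The protocol has chosen not to enrol pregnant women as patients. A woman who plans to conceive within the treatment month passes the patient list, and she could then be needled while in a state that would have barred her at entry. No estimand, test or sample size depends on this.

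**Working it through.** There is no planned figure to reproduce. The check sets the two lists side by side and reads them against Table 1.

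**1. The lists compared**

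| | Healthy controls (2.4.2) | Tinnitus patients (2.3.2) |
|---|---|---|
| Currently pregnant | excluded | excluded |
| Currently breastfeeding | excluded | excluded |
| Planning childbearing within 6 months | excluded | not mentioned |
| Acupuncture sessions | 0 | 10 |

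**2. Other places a rule could stand.** The inclusion criteria, Table 1, the intervention sections (2.6.1 and 2.6.2) and the safety section (2.10) contain no pregnancy test, contraception requirement or rule on conception during the study. In the article, item 8 is the whole of the provision for patients.

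**3. Time in the study**, from the week labels in Table 1, counted from the Week −1 screen:

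- to the last treatment week: 4 − (−1) = 5 weeks
- to T1, the last control assessment: 5 − (−1) = 6 weeks
- to T2, patients only: 13 − (−1) = 14 weeks

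Section 2.7 counts the 8-week follow-up from the start of treatment, which would bring T2 earlier, so 14 weeks is the longest reading.

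Six months is about 26 weeks. For a control, the rule reaches about 26 − 6 = 20 weeks past her last assessment. For a patient, the same rule would cover the whole of participation, since 26 exceeds 14. A rule ending at T1 would cover all the needling.

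**4. A worked case.** Take a woman of 30 who is neither pregnant nor lactating at Week −1, intends to conceive in the coming month and meets every other criterion. Under section 2.4.2 she cannot be a control. Under section 2.3.2 she meets no exclusion, and the entry rule then qualifies her as a patient. Table 1 shows no second eligibility check before or during W1 to W4.

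**The case against.** Several points on the other side have force.

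- **The lists need not match.** They govern different populations and differ elsewhere: metallic implants are named only for controls, serious systemic illness only for patients. No sentence in the article is contradicted. This stands. It is why the point concerns an unexplained and oddly placed difference and not a false statement.
- **No hazard is stated.** A reader might infer, especially from the lower-abdominal points Qihai (CV6) and Guanyuan (CV4), that the protocol regards needling in pregnancy as dangerous. The documents do not support that. Pregnant and breastfeeding women are also barred from the control group, which is never needled, so the exclusion could reflect general caution about research participation or about the measurements. This stands in full.
- **Pregnancy during the study may be handled elsewhere.** A reader might infer that a patient who conceives would go on being treated. The article does not say so. Item 8 carries no time limit, and repeat testing, contraception advice or a stopping rule could be in the full protocol. This also stands. Such rules would reduce the exposure, but they would not alter who is admitted under the two printed lists.
- **Other protections exist.** Participants are told of risks, may withdraw at any time, and have adverse events recorded through W5. These respond to events after entry and do not settle who should enter.

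**Conclusion.** The inconsistency is real as printed. Women planning childbearing are excluded where there is no intervention and admitted where there is one, although pregnant women are kept out of the treated group. This rests only on the two lists, the entry rule and Table 1, and on the ordinary reading that item 8 is applied at the single marked eligibility screen.

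The point is minor. It carries no claim of bias, lost power or altered results. The lists do differ on a factor unrelated to tinnitus, but nothing in the documents suggests that this would shift the ABR comparison. Nor can the number of patients affected be sized: any count of expected conceptions would need the share of patients planning pregnancy and a conception rate, and the documents give neither. What can be counted is exposure, not harm: 10 sessions per patient and none per control.

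**What to change.** Extend section 2.3.2 item 8 so that, besides intolerance of acupuncture, it excludes *pregnant or lactating women, and those planning to conceive before the post-treatment assessment (T1)*. Reusing the 6-month control wording would also close the gap and make the lists agree, at the price of a restriction longer than the treatment period requires. The control item can stay, though a short reason for its 6-month span would help, since controls finish at T1.

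The cost is one line in the exclusion list and the screening form, with notice to the ethics committee, which section 2.1 already requires for design amendments. Eligibility narrows slightly, and the treated sample would no longer include women planning a pregnancy in the near term. The extra screening depends on a share that the documents do not give. If, as an assumption, 1 to 4 of every 36 otherwise eligible patients were refused, enrolling 36 would take 36 / (1 − 1/36) = 37.0 to 36 / (1 − 4/36) = 40.5 such patients, that is about 1 to 5 more.

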### Audiological assessments

2.5

Pure-tone audiometry will be performed using an AC40 clinical audiometer (Interacoustics A/S, Middelfart, Denmark) with TDH-39 supra-aural headphones and a B-71 bone conductor, in a sound-attenuated booth complying with ISO 8253-1 standards. Air conduction thresholds will be obtained at 0.125, 0.25, 0.5, 1, 2, 4, and 8 kHz, and bone conduction thresholds at 0.25, 0.5, 1, 2, and 4 kHz, using the modified Hughson-Westlake procedure. The PTA will be calculated as the average of thresholds at 0.5, 1, 2, and 4 kHz. Individual frequency thresholds and the configuration of the audiogram (i.e., flat, sloping, high-frequency dip, or notch at 4000 Hz) will be recorded and described for both groups.

Tympanometry and acoustic reflex testing will be performed using an Interacoustics Titan IMP440 impedance system (Interacoustics A/S, Middelfart, Denmark). Tympanometry will be conducted using a 226 Hz probe tone to assess middle ear compliance and pressure. Acoustic reflex thresholds will be measured ipsilaterally and contralaterally at 500, 1,000, 2,000 and 4,000 Hz.

Distortion product otoacoustic emissions (DPOAEs) will be recorded using an Interacoustics Titan DPOAE440 system (Interacoustics A/S, Middelfart, Denmark). DPOAEs will be measured to assess outer hair cell function, and will be recorded across a frequency range of 1–8 kHz (1/3 octave steps) using primary tone levels of L1 = 65 dB SPL and L2 = 55 dB SPL (f2/f1 ratio = 1.22). A DPOAE response will be considered present if the signal-to-noise ratio (SNR) is ≥6 dB at the corresponding frequency. DPOAEs will be considered normal if responses are present at ≥6 of the 8 tested frequencies (1, 1.5, 2, 3, 4, 5, 6, and 8 kHz). Notably, absent DPOAEs at high frequencies (≥6 kHz) may occur in asymptomatic individuals with normal pure-tone thresholds and do not necessarily indicate pathology; such findings will be documented but will not automatically exclude participants unless accompanied by other abnormalities.

Tinnitus Handicap Inventory (THI) will be administered using the validated Chinese (Mandarin) version (32).

### Intervention

2.6

#### Treatment course

2.6.1

All chronic tinnitus patients will receive a total of 10 acupuncture sessions, administered once every 2 days (three times per week) over a period of 4 weeks. Based on our prior research and clinical experience using acupuncture to treat tinnitus, we selected a total of 10 acupuncture sessions (33, 34). These methods are thought to be representative and appropriate for assessing acupuncture’s effectiveness in treating persistent tinnitus.

Patients will be observed at week eight after completing 10 sessions in order to more fully assess the long-term efficacy of acupuncture treatment.

#### Acupuncture program

2.6.2

##### Acupuncture points prescription

2.6.2.1

Based on the clinical expertise of senior acupuncturists and the results of earlier relevant investigations, the acupoint prescription for this study was created (35). The selected acupoints are as follow: Yifeng (bilateral), Tinggong (bilateral), Tinghui (bilateral), Zhongwan, Xiawan, Qihai, Guanyuan, Yindu (bilateral), Shangqu (bilateral), Huaroumen (bilateral). Licensed acupuncturists with over 10 years of clinical experience will deliver all treatments. Before the experiment, all practitioners will receive standardised instructions to ensure protocol adherence. A brochure outlining the standardized operating procedures will be provided to each practitioner. Table 2 summarizes the precise positions of each acupoint, which will be identified in accordance with the WHO Standard Acupuncture Point Locations (36).

**Table 2 tab2:** Acupoint positions.

Acupoints	Position
Yifeng (TE17)	In the anterior region of the neck, posterior to the ear lobe, in the depression anterior to the inferior end of the mastoid process.
Tinggong (SI19)	On the face, in the depression between the anterior border of the centre of the tragus and the posterior border of the condylar process of the mandible.
Tinghui (GB2)	On the face, in the depression between the intertragic notch and the condylar process of the mandible.
Zhongwan (CV12)	On the upper abdomen, 4 B-cun superior to the centre of the umbilicus, on the anterior median line.
Xiawan (CV10)	On the upper abdomen, 2 B-cun superior to the centre of the umbilicus, on the anterior median line.
Qihai (CV6)	On the lower abdomen, 1.5 B-cun inferior to the centre of the umbilicus, on the anterior median line.
Guanyuan (CV4)	On the lower abdomen, 3 B-cun inferior to the centre of the umbilicus, on the anterior median line.
Yindu (KI19)	On the upper abdomen, 4 B-cun superior to the centre of the umbilicus, 0.5 B-cun lateral to the anterior median line.
Shangqu (KI17)	On the upper abdomen, 2 B-cun superior to the centre of the umbilicus, 0.5 B-cun lateral to the anterior median line.
Huaroumen (ST24)	On the upper abdomen, 1 B-cun superior to the centre of the umbilicus, 2 B-cun lateral to the anterior median line.

##### Acupuncture procedures

2.6.2.2

The patients will be placed in a supine position. Acupuncture needles (Hwato brand, Suzhou Medical Devices, China) measuring 50 mm in length and 0.30 mm in diameter will be utilized for the three periauricular acupuncture points (Tinggong, Tinghui, and Yifeng) following a standard disinfection of the surrounding skin. The needles for Tinggong and Tinghui will be inserted to a depth of about 20 to 25 mm, vertical to the skin. The needle tip for Yifeng will be inserted at a 45° angle and pointed anterosuperiorly in the direction of the ear canal. The needle will be gently inserted to a depth of approximately 20–25 mm, followed by manipulation with small-amplitude, low-frequency twisting (amplitude 180°, frequency <60 times/min) to elicit the De Qi sensation. When the patient reports a distinct sensation of soreness, numbness, or distension radiating into the ear canal, the manipulation is continued. Acupuncture needles (40 mm in length, 0.25 mm in diameter) will be used for limb acupoints, with lifting-thrusting and even twisting techniques. The Chinese Modified Massachusetts General Hospital Needle Sensation Scale (C-MASS) will be used to measure the degree of needle sensation. Each needle is stored for 30 minutes.

#### ABR data collection

2.6.3

The Interacoustics Eclipse EP25 auditory evoked potential system (Interacoustics A/S, Middelfart, Denmark) with click acoustic stimulation will be utilized for recording auditory brainstem responses. Every recording will take place in a calm, sound-attenuated, electrically insulated space that is kept at a suitable temperature. At the beginning of the experiment, subjects will be asked to lie in a supine position in a comfortable state and to remain relaxed or fall asleep if possible. The ambient noise level in the sound-attenuated room will be maintained at ≤30 dB(A). The skin should be cleansed with a scrub before electrode application. The ground electrode is located at the low forehead, the reference electrodes on either side of the mastoid process, and the recording electrode at midline of the forehead close to the hairline. Electrode impedance should not exceed 3 kΩ.

*Stimulus and recording parameters*: The stimulus will be a 0.1 ms square-wave click with alternating polarity (rarefaction and condensation) to minimize stimulus artifact. The stimulus repetition rate will be 11.1 clicks per second (Hz), chosen because it produces stable and reproducible ABR waveforms with minimal neural adaptation effects, and it is a standard default rate widely used in clinical and research settings (37). The maximum stimulus intensity will be 100 dB nHL. Bandpass filter settings: Low-pass: 1,500 Hz, High-pass: 33 Hz, 6/oct. Artifact rejection: Sweeps containing activity exceeding ±40 μV will be automatically rejected. Analysis time window: A 10 ms post-stimulus epoch will be recorded. Number of sweeps: A minimum of 1024 artifact-free sweeps will be averaged for each waveform, with duplicate recordings obtained to ensure reproducibility.

*Stimulus ear*: For patients with bilateral tinnitus, ABR will be recorded separately for each ear using monaural click stimulation with contralateral white noise masking (at 40 dB below the stimulus level) to prevent crossover responses. The order of ear testing will be randomized across participants.

*Analytical strategies*: Two complementary analytical approaches will be employed. First, ABR thresholds will be determined by descending intensity series starting from 100 dB nHL in 10 dB decrements, with the threshold defined as the lowest stimulus intensity at which a reproducible wave V can be visually identified. Second, supra-threshold ABR waveform parameters will be analyzed at a fixed intensity of 100 dB nHL, including peak latencies (waves I, III, and V), wave amplitudes, and inter-peak latencies (I–III, III–V, and I–V).

A minimum of two stable waveforms with good reproducibility will be obtained at maximum intensity and at threshold. All waveforms and data will be independently interpreted and analyzed by two licensed audiologists who will remain blinded to group allocation.

